### **C.3 Community Outreach and Education**

The legislation that created the funding for the H. Lee Moffitt Cancer Center included the mandate that it serve all the residents of Florida, regardless of race, ethnicity, or socioeconomic status. [name] directs the Outreach and Education Office, and has established a variety of approaches to accomplish this goal. Several funded educational activities exemplify [name] ongoing focus in the area of cancer communication strategies to reduce health disparities.

*C.3.1 Cancer, Culture, and Literacy. -* In 1998, [name] initiated the national biennial Cancer, Culture, and Literacy Conferences that aim to improve care across the continuum of cancer control by enhancing the knowledge and skills of professionals responsible for creating multicultural, multilingual, and literacy-sensitive communications. This national meeting, supported by CDC, NCI, CRCHD, Pfizer and the Cancer Research and Prevention Foundation, continues to gain high national recognition as a forum for the exchange of knowledge about the nexus of cancer, culture and literacy and involves extensive interactions with many national scholars and developing investigators. The initial conference spurred the creation of the Cancer, Culture and Literacy Institute, an NCI funded R25 education project (CA 90654). The goals are accomplished through the following educational activities: a) a five-day intensive institute in Tampa, Florida, b) an ongoing Web-based continuing education curriculum, and c) ongoing interactions between scholars/mentors and participants driven by the integration of cancer, culture and literacy themes. To date (Years 01-03), 64 doctoral prepared individuals from a wide array of disciplines (medicine, nursing, psychology, social work, medicine, adult education, nutrition, physical therapy, epidemiology, anthropology, etc.) have participated in this program. Of these 64, approximately 53% were minority (American Indian/Alaska Native 6%, Asian 14%, Hispanic 14%, Native Hawaiian/Pacific Islander 3%, Black/African American 22%, More than one race 3%).

*C.3.2 Multilingual Cancer Education and Outreach for Medically Underserved and Priority Populations -* [name] has successfully developed a number of programs in this arena. The first targeted Hispanic migrant seasonal farm workers and low income women. Entitled *Por Su Salud*, and funded by an Avon grant, it allowed for the creation and dissemination of culturally appropriate Spanish language materials based on extensive formative research and testing. Each year, a total of 1,000 Hispanic migrant and seasonal farmworkers and low-income rural women are reached with culturally appropriate screening mammography, clinical breast examination and breast health educationand this program was consider one of ten model national programs. The second innovative project, funded by the Cancer Research Foundation of America, was entitled ¡Platiquemos Sobre Su Salud!/Let’s Talk About Your Health! This consisted of the development and evaluation of a Spanish-language breast and cervical cancer educational videotape intervention in terms of knowledge, satisfaction, comfort level, and intentional and actual breast/cervical cancer screening practices among Hispanic migrant and seasonal farm worker women. Reactions to the educational tool were highly favorable and knowledge increased (p<.001). Findings suggested that appropriate educational tools could meet the information needs of at-risk (multicultural, multilingual and low-literacy) populations and contribute to adherence to breast and cervical cancer screening behaviors[59, 60].

*C.3.3. National Work Groups Related to Cancer and Disparities*-[name] was one of the pioneers who served on the National Cancer Institute’s initial Work Group for Cancer and Literacy (1995-1998) and was a member of NCI’s Comprehensive Working Group on Informed Consent in Cancer Clinical Trials (1996-1998) that addressed cancer information needs of diverse literacy populations and developed policy statements and informed consent guidelines[61].Most recently, [name] served as a member of the Institute of Medicine’s Committee on Health Literacy. The outcome of this 18-month activity was the 2004 release of *Health Literacy: A Prescription to End Confusion* in March, 2004. This expertise will be invaluable to the proposed study.

### **C.4 Patient Satisfaction**

[name] has been involved in numerous studies evaluating quality of life and patient satisfaction in people with cancer. With regard to quality of life, much of this work has focused on women receiving treatment for breast cancer. Early research consisted of cross-sectional studies comparing the quality of life of specific subgroups of breast cancer survivors to the quality of age-matched women with no history of cancer. These studies documented that, relative to women with no history of cancer, quality of life was poorer in women with breast cancer who had previously been treated with standard dose adjuvant chemotherapy[62] or high dose chemotherapy followed by stem cell rescue [63], but not radiotherapy only. [64] [name] has generated similar findings with regard to the experience of fatigue in these same subgroups of breast cancer survivors. [62-64] In collaboration with [name], [name] has also evaluated the relationship of functional impairment to economic well-being in breast cancer survivors. [65] Findings indicated that breast cancer survivors were more likely to be functionally impaired than age-matched women with no history of cancer and that impaired women, in turn, were more likely to reduce work effort and experience downturns in market earning.

With regard to patient satisfaction, work has focused on developing and implementing a cancer-center wide system for assessing patient satisfaction in individuals receiving either inpatient or outpatient care. Beginning in 1999, a group led by [name] began meeting to solicit input from relevant stakeholders regarding the format and content of a patient satisfaction survey. The group also conducted a review of existing patient satisfaction surveys used with cancer patients. These activities led to the development of a survey that was then pilot tested and finalized. Questions are designed to elicit information about all levels and all aspect of care patients are likely to encounter during either inpatient stays or outpatient visits. This survey is currently administered twice a year to patients randomly selected from among those seen in the outpatient clinics of each of Moffitt Cancer Center’s 14 clinical programs and in each of the center’s 6 inpatient units. Surveys are administered by telephone by trained personnel who enter responses directly into computer files. Over 2,000 patients per year are surveyed using these methods. Summaries of results for specific cancer center units are provided monthly to administrators and faculty members and are then utilized to initiate and evaluate the success of continuous quality improvement projects. Semi-annual reports are used to compare patient satisfaction across clinical programs and across inpatient units. In addition to telephone-administered surveys, focus groups are conducted periodically with patients to explore new areas not addressed in the survey and to allow for more in-depth exploration of relevant issues. Approximately 60 patients per year participate in focus groups. A manuscript describing the development and current operation of this patient satisfaction survey system is currently in press.[66]

### **C.5 Health Choice Network**

Health Choice Network and its member community health centers have extensive experience in serving and working with diverse populations. Located in low-income and predominantly Black and Hispanic communities, most of the Network’s member community health centers have been providing comprehensive primary and preventive health care to racially and ethnically diverse populations for several decades. Overall, 30 percent of community health centers patients in 2001 were Black and 42 percent were Hispanic. Community health centers are required by statute to have Boards of Directors on which at least 50 percent of members are members of the community served and patients. This ensures that the communities served by the centers have a strong voice, and that the centers remain closely tied to the diverse populations they serve. Representation of minorities on the staff and governing Board of Health Choice Network is strong. Of Health Choice Network’s four-member Executive Team, consisting of the President/Chief Executive Officer, two Vice Presidents, and the Chief Financial Officer/Chief Information Officer, one is African American and one is Hispanic. Health Choice Network’s governing Board consists of Chief Executive Officers/Chief Administrators of each member community health center and clinical representatives or Board members from several other member centers. 7 of the 12 members (58%) of Health Choice Network’s Board of Directors are African American and 2 (17%) are Hispanic.

Through centralized program development efforts, Health Choice Network has the capacity to plan, manage, seek grant funding for, evaluate and replicate community-based health promotion and disease prevention initiatives at a higher level than member health Centers would be able to achieve individually. Under the leadership of the Program Development Unit, the Network’s member Centers, along with church leaders in their communities and other partners, have developed and implemented Healthy Body, Healthy Soul, a community-based health promotion and disease prevention program. The mission of the program is to increase access to health care and improve health in predominantly African-American and Hispanic communities through collaboration with churches and other community partners.

The key features of the Healthy Body, Healthy Soul Program include: 1) core partnerships between community health centers and the faith-based community; 2) community capacity building (education and training of staff and partners); 3) the use of Lay Health Educators to conduct effective community screening, outreach, and patient support; 4) access to regular primary and preventive health services; 5) comprehensive disease and case management services; and 6) patient and family education. The core partnership between community health centers and churches is based on the conviction that collaboration between community-based health care providers and the faith community holds great potential as a strategy for conducting effective outreach, pursuing innovative approaches to health education and promotion, and delivering other community-based interventions. As spiritual leaders, clergy members have influence and relationships of trust in their communities, positioning them to reach out to community members effectively with health information that empowers people to make changes in their lives.

Distinctive features of the Program include core partnerships between community health centers and the faith-based community and the use of Lay Health Educators (LHE) to conduct effective community screening, outreach, and patient support. The implementation of the Program occurs on three organizational levels, involving the Network, Centers and faith partners. The Network is the first level of organization and provides overall management, oversight, and evaluation of Healthy Body, Healthy Soul Programs. Centers are the second level of organization and provide primary care, referrals to specialty care, case management, health education and links to social services. Faith partners provide a third level of organization and focus on identifying, screening, and referring community residents to needed health care. They provide the following critical services: 1) cultivating support among other community and faith-based organizations; 2) recruiting and supervising LHE and volunteers; 3) planning/coordinating monthly “Healthy Sunday” events fostering “fellowship of screening” activity; 4) hosting community educational activities; and 5) spiritual counseling. This innovative program will play a key role in the dissemination of the Patient Navigator Program developed and tested in Phase I and II.

### **C.6 The American Cancer Society and Reach to Recovery**

The American Cancer Society (ACS) is a nationwide community-based voluntary health organization dedicated to eliminating cancer as a major health problem by preventing cancer, saving lives, and diminishing suffering from cancer through research, education, advocacy, and service. With more than two million volunteers nationwide, the American Cancer Society is one of the oldest and largest voluntary health agencies in the United States. The Florida Division has more than thirty offices to serve local communities, and 80,000 volunteers directing the Society’s programs at the local level. These dedicated volunteers donate their time and talents to further cancer research; educate the public about early detection and prevention; advocate for responsible cancer legislation in the local, state, and federal governments; and serve cancer patients and their families to help make the cancer experience a little easier.

In the ACS Reach to Recovery Program, breast cancer survivors provide one-on-one support and information to help individuals cope with breast cancer. Specially trained survivors serve as volunteers, responding in person or by phone to the concerns of people facing breast cancer diagnosis, treatment, recurrence or recovery. There are currently over 60 Reach to Recovery volunteers in the Tampa Bay area. Our design will capitalize on this existing resource of trained volunteers to augment the Navigator Program.

# D. MATERIALS AND METHODS

The overall research design of the Patient Navigator Program is presented in figure1 (D.1). We follow with a description of the study population (D.2) and an overview of Phases I (D.3), II (D.4) and III (D.5). Finally, we end with the timeline for the proposed project (D.6).

**D.1 Overview**

**
[figure not shown]
**

**D.2. Study Population and Inclusion/Exclusion Criteria**

Hillsborough County, the fourth most populous county in Florida (population 1,027,318), encompasses metropolitan Tampa, its surrounding suburbs, and primarily rural areas to the west and south. Hillsborough County has a diverse population including populations noted for disparities in cancer care and outcomes (Hispanics, African Americans, patients residing in rural settings).

This project will originally target clinics that specifically provide primary care to disadvantaged populations within Hillsborough County. Two of these clinics (Tampa General Health Clinics) are located in inner city Tampa, serving primarily minority and lower socioeconomic populations. Three clinics (Suncoast Community Health Centers) are located in primarily rural areas of Hillsborough County, for which Hispanic patients and migrant farm workers are important populations served.

Each of these clinics has previously participated in an NCI-funded intervention (Cancer SOS Project, summarized in C.2) to promote cancer screening in primary care clinics serving disadvantaged populations. The investigative team has an excellent working relationship with clinic administrators and primary care providers. The SOS project also led to a better understanding of the relevant barriers to screening and appropriate follow-up care, which contributes to the feasibility of the proposed study. A brief description of the clinics, and a summary table of their key characteristics are as follows.

*Tampa General Healthcare (TGH)-* Tampa General Hospital is a private not-for-profit corporation governed by a volunteer Board of Directors. As a teaching facility affiliated with the University of South Florida College of Medicine, Tampa General partners with academic and community institutions to support both their teaching and research missions. As the region’s leading safety net hospital, TGH is committed to providing high quality health services to all residents. TGH operates five ambulatory care clinics, two of which are located in inner city Tampa.

*Suncoast Community Health Centers -* Three clinics serve the Suncoast Community Health Center, Inc. network. The clinics are located in three cities each located approximately 20 miles outside the Tampa Metropolitan Area.

| Table D.2. Characteristics of participating community health centers in Tampa region | | | | | | |
| --- | --- | --- | --- | --- | --- | --- |
| Clinic Name | Screening Visits  # per year | African American  (%) | Hispanic  (%) | Under-insured  (%) | Low literacy  (%) | Spanish speaking  (%) |
| Ruskin | 33,800 | 5 | 50 | 85 | 40 | 30 |
| Plant City | 26,000 | 30 | 40 | 85 | 65 | 45 |
| Dover | 36,400 | 0 | 75 | 100 | 50 < 6th gr | 75 |
|  |  |  |  |  |  |  |
|  |  |  |  |  |  |  |
| Health Park | 20,800 | 40 | 20 | 70 | 40 | 5 |
| Midtown | 19,500 | 35 | 35 | 85 | 30 | 5 |

Since the start of the project, the number of participating clinics has increased (n=12) and they have been randomized as described below. Note that randomization occurred within sponsoring organization and for organizations with an odd number of clinics randomization was performed to insure that there were a greater number of intervention clinics than control.

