**Tampa General Health Care**

TGH Family Care Center Healthpark

(30th Street) Intervention

TGH Family Care Center Kennedy Control

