**Suncoast Community Health Centers**

Ruskin Health Center Intervention

Plant City Family Care Intervention

Dover Health Center Control

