### **D.3.3 Baseline Data Collection**

We will collect baseline data from all participating clinics. Subjects will be eligible for medical record abstraction if they were seen at one of the participating clinics within one year of the clinic’s start in the project and if the subject has a breast or colorectal screening abnormality that meets eligibility criteria (see above). Specific data elements that will be collected are listed in the NOVA data dictionary (Breast - Table 7, Colorectal -Table 9).

Questions to be addressed using baseline data include:

*1. What is the average length of time from abnormal screening test to definitive diagnosis?*

*2. Are there any predictors of timeliness of diagnosis?*

For patients diagnosed with cancer, the following additional questions will be addressed.

*1. How many breast and colorectal cancers are diagnosed each year?*

*2. At what stage are these cancers diagnosed?*

*3. What is the average length of time from abnormal screening test to definitive diagnosis?*

*4. What is the average length of time from diagnosis to initiation of definitive treatment?*

*5. For each treatment modality (surgery, radiation therapy, chemotherapy), what percentage of patients is recommended to have treatment and what percent complete this therapy?*

*6. What physicians/ facilities currently provide diagnostic and cancer care?*

Baseline data will be helpful in establishing baseline estimates of project outcomes, confirming sample size requirements, and suggesting navigation strategies. Chart abstractions will be conducted on the clinic premises and no information that could uniquely identify a patient will be recorded. Thus the final dataset will be de-identified for human subjects purposes.

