###### **D.4.3 Patient Recruitment**

As described previously, seven clinics will provide the Navigator Program and five clinics will not provide the Navigator Program based on random assignment. A description of the Navigator Program to be provided at those clinics randomized to this condition follows. We will make no attempt to alter the delivery of services at those clinics not randomized to deliver the Navigator Program. Rather, we will use both observational and survey methods to characterize the processes that typically occur in these clinics once patients are identified as having a breast or colorectal abnormality. These data will be used to characterize the extent to which delivery of care differed in our two intervention conditions.

The eligibility criteria were defined in D.2.1 above. Subjects having cancer-related abnormalities will be identified by research assistants using a variety of methods. Methodologies for identifying patients will be refined and pilot tested in the project’s first year. Procedures for subject identification and recruitment will be identical for intervention and control clinics. Once identified, patients will be contacted by research assistants for recruitment into the study. Research assistants will use the following sources to identify patients:

*Appointment records*: Appointment records provide the reason for each patient’s visit and will be assessed weekly by research assistants. This information will be used to identify cancer related symptoms (i.e. breast lumps, rectal bleeding).

*Screening logs*: Participating clinics maintain screening logs to document completion of cancer screening tests such as Pap smears, mammograms, and FOBT. Research assistants will track screening logs on a weekly basis to identify patients having abnormal results on mammography or FOBT.

*Referral coordinators*: Research assistants will also make at least weekly contact with referral coordinators at each clinic to identify patients who may have been referred for cancer related problems.

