**D.4.7.b Statistical Analysis and Study Power**

The statistical analyses will focus on those subjects receiving an abnormal or suspicious mammogram (BIRAD 0, 4, or 5) and those with abnormal FOBTs or abnormalities detected on sigmoidoscopy (see D.2.1). Those in the Navigator intervention groups will be compared to those in the control groups with respect to two outcomes. For patients with breast or colorectal abnormalities, the primary outcome will be time from detection of abnormality to definitive diagnosis, measured as a continuous variable. In addition, we will assess the proportion of patients who successfully complete an appropriate diagnostic evaluation. The records of each subject with such an indication for follow-up will be examined as described in D.3.3.

Study power is based on the following factors. The primary endpoint is ‘Length of time’ (LOT=time from screening to definitive diagnosis). Suppose LOT follows a normal distribution (mean=30 days, “std” = standard deviation). Then, to detect the difference in LOT between two groups (navigator versus control groups), a two-sample t-test will be used. The required minimum sample size to achieve 80% statistical power is calculated based on the t-test and illustrated in Figure 1.

For example, group sample sizes of 29 and 29 (total 58) achieve 80% power to detect a difference of 10 days between the null hypothesis that both group means are 30.0 and the alternative hypothesis that the mean of Navigator group is 20 days with estimated group standard deviations of 15.0 each and with a significance level of 0.05 using a one-sided two-sample t-test. However, to detect a difference of 5 days with the same standard deviation 15.0 between the two groups, one would need at least 112 samples for each group (total 224).

Figure 1. Required sample sizes for each group based on the expected mean of navigator group by the standard deviation. For the control group, the mean value of LOT was set up as 30.0. The standard deviations for both groups are assumed to be equal. α=0.05 (one sided: mean 1 > mean 2).

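### Clinics were allocated 2:1 or 1:1 depending on organisation, but every arm comparison the protocol names ignores organisation, so the pooled estimate carries a small bias built in by the design

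*Protocol*

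**What the plan says.** D.2 states that allocation was done separately inside each sponsoring organisation, and that "for organizations with an odd number of clinics randomization was performed to insure that there were a greater number of intervention clinics than control". D.4.2 had already fixed this pattern for the first five clinics: two of three at Suncoast and one of two at Tampa General were to start navigation at once. The clinic lists in D.2 show the result:

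| Organisation | Intervention | Control |
| --- | --- | --- |
| Tampa General | 1 | 1 |
| Suncoast | 2 | 1 |
| Premier | 1 | 1 |
| Manatee | 2 | 1 |
| Pinellas | 1 | 1 |
| Total | 7 | 5 |

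The single control entries include "TGH Family Care Center Kennedy Control" and "Dover Health Center Control". D.4.3 confirms the totals: "seven clinics will provide the Navigator Program and five clinics will not provide the Navigator Program based on random assignment".

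For the comparison of time to diagnosis between arms, D.4.7.b says that "a two-sample t-test will be used". It adds a log-rank test for the Kaplan-Meier curves and a Wilcoxon rank sum test for guideline adherence. None of these is described as stratified or adjusted.

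D.3.3 plans to abstract time to diagnosis at every clinic before the trial. Its stated use is: "Baseline data will be helpful in establishing baseline estimates of project outcomes, confirming sample size requirements, and suggesting navigation strategies". Adjusting the arm comparison is not among the uses.

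**The concern.** A clinic's chance of being an intervention clinic is 2/3 in a three-clinic organisation and 1/2 in a two-clinic one. When allocation probability differs by stratum, an analysis that pools over strata attributes part of the difference between strata to treatment. This is not chance imbalance that a further randomisation would even out, because the organisation mix of each arm is fixed by the design.

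D.2 gives some reason to expect differences. It describes the Suncoast clinics as mainly rural, with 40 to 75% Hispanic patients and 30 to 75% Spanish-speaking. The Tampa General clinics are described as inner-city, and the two in Table D.2 show 20 to 35% Hispanic and 5% Spanish-speaking. If times to diagnosis differ between the two types of organisation, the primary estimate is shifted and the error rate of its test is no longer the nominal one.

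**Working it through.** **The plan's own figures.** These are the SD of 15 days, one-sided alpha of 0.05 and power of 80% in D.4.7.b. The normal approximation n = 2 × 15² × (1.645 + 0.842)² / δ² gives 27.8, so 28 per group, for δ = 10 days, and 111.3, so 112 per group, for δ = 5 days. The exact t calculation gives 29 and 112, as stated. The design effect 1 + 99 × ICC gives 1.99, 2.98 and 4.96, which matches the table.

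**Imbalance between arms.** Three-clinic organisations supply 4/7 = 57.1% of intervention clinics and 2/5 = 40.0% of control clinics. The difference is 0.171.

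**Expected shift.** With equal enrolment per clinic (assumed), each three-clinic organisation has net weight 2/7 − 1/5 = +0.086 in the pooled difference, and each two-clinic organisation has 1/7 − 1/5 = −0.057. Summed, this is 0.171 × D, where D is the mean for three-clinic organisations minus the mean for two-clinic ones.

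**How large D can be.** The protocol gives no times by organisation, but its SD and ICC set a ceiling. Six clinics fall in each type, so a type difference D alone contributes D²/4 to the between-clinic variance. Taking 15 days as the total SD:

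| ICC | Between-clinic variance | Largest D (days) | Largest shift (days) |
| --- | --- | --- | --- |
| 0.01 | 2.25 | 3.0 | 0.51 |
| 0.04 | 9.00 | 6.0 | 1.03 |

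Taking 15 days as the within-clinic SD instead gives a variance of 0.04/0.96 × 225 = 9.4 at ICC 0.04, a D of about 6.1 and a shift of about 1.05. These ceilings assume that organisation type explains all between-clinic variation. If at ICC 0.04 that variation lay between organisations at random, the SD of D would be √(9 × (1/2 + 1/3)) = 2.7 days and the typical shift about 0.5 day.

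**Effect on the t-test.** With 100 patients in each of 12 clinics (assumed), the standard error is 15 × √(1/700 + 1/500) = 0.88 day. With no true effect, a shift of 0.51 or 1.03 days favouring navigation raises the one-sided 5% rejection rate to 1 − Φ(1.645 − 0.51/0.88), about 15%, or 1 − Φ(1.645 − 1.03/0.88), about 32%. A shift the other way lowers it to about 1.3% or 0.2% and hides part of a real effect.

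**What organisation terms do to precision.** Let c be the clinic variance and o the organisation variance. The pooled clinic-level contrast has variance 0.343c + 0.0245o. With organisation fixed effects it is c/(3 × 1/2 + 2 × 2/3) = 0.353c. Adjustment lowers the true variance only when o/c exceeds (0.353 − 0.343)/0.0245, about 0.41. Residual degrees of freedom fall from 12 − 2 = 10 to 12 − 6 = 6.

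Simulated clinic-level power for a 5-day effect at ICC 0.04 (12 clinics of 100, 5,000 runs):

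| Share of between-clinic variance due to organisation | Unadjusted | Organisation-adjusted | Baseline-adjusted |
| --- | --- | --- | --- |
| 0% | 77% | 73% | 95% |
| 50% | 82% | 89% | 96% |
| 80% | 86% | 98% | 97% |

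The baseline column assumes 60 charts per clinic and a clinic effect that is fully stable over time, which is a best case. The simulation draws organisation effects at random around zero, so the shift averages out across runs. In the one real set of five organisations it does not.

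**The case against.** The strongest reply is that the t-test sentence stands in the power paragraph, and that strata and covariates of the primary model are commonly left to an SAP, which was not available here. Part of this stands: an SAP may already stratify. But D.4.7.b does name its tests, for the primary and the secondary comparisons, and nothing in the protocol ties any of them to the randomisation strata.

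Four stronger readings are tempting, and the protocol does not support them.

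- A reader might infer that the bias could equal the 5-day effect in the power section. That needs D of about 30 days, the whole assumed control mean, and an ICC of about 0.50, far above the protocol's range.
- A reader might infer that arm is confounded with organisation outright. Every organisation has clinics in both arms, so only 17% of a difference between types enters. The demographic contrast is documented only for Suncoast and Tampa General, and no times are given for any organisation.
- A reader might infer that ignoring organisation necessarily loses precision. The table above shows it can go either way.
- A reader might infer that the baseline times are in hand and that leaving them out is an error. D.3.3 plans the abstraction, on other, de-identified patients, so it can supply only a clinic-level mean. Its value depends on a correlation with trial-period times that the protocol does not give. Using it is an option, not a requirement.

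Ignoring clustering by clinic is a separate and larger fault. In the same simulation with no effect and no organisation variance, the patient-level t-test rejects in 17% of runs at ICC 0.02 and 24% at ICC 0.04. Correcting the standard error for clinics would not remove the shift described here.

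**Conclusion.** The point holds in a limited form. The allocation ratios differ by organisation, the named comparisons pool over organisation, and the pooled estimate therefore carries 0.17 × D by design. On the protocol's own SD and ICC range this is at most about 0.5 to 1.0 day. It is modest beside the 5- and 10-day effects in the power section, but of the same order as the 0.88-day standard error of the patient-level t-test. The direction is unknown, and the shift is zero if the two types of organisation have equal times. The size rests on equal enrolment per clinic, about 100 patients in each of 12 clinics, and an ICC no higher than 0.04; a higher ICC would allow a larger shift. The correction is worth making because it is cheap and removes the bias completely under the usual assumption of additive organisation effects.

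**What to change.** In D.4.7.b, state that the primary comparison follows the randomisation. Two routes are available:

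- A clinic-level or mixed-model analysis with the five organisations as strata and few-cluster degrees of freedom.
- A permutation test within organisation. There are 2 × 3 × 2 × 3 × 2 = 72 allocations, so the smallest one-sided p is 1/72 = 0.014. The point estimate should still be formed within organisation.

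Stratify the log-rank and Wilcoxon tests by organisation as well. Stratification alone does not deal with clustering by clinic, so their p-values need the same permutation or another allowance for clinic. Optionally, add each clinic's planned Phase I mean time to diagnosis as a clinic-level covariate, chosen before outcome data are seen.

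The cost is wording and analysis time; no further patients or data are needed. Between-clinic degrees of freedom fall from 10 to 6, or to 5 with the baseline covariate. Power can drop slightly if organisations do not differ (77% to 73% in the simulation). The permutation test is coarse: only three of the 72 allocations fit within one-sided 0.05 (3/72 = 0.042). If an SAP already specifies such an analysis, the protocol text should be brought into line with it.
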